### Study interventions

2.6

Following enrollment, all patients will receive a PBF during the run-in phase (study days 1–3). On study day 4, gastrointestinal function will be reassessed. Participants meeting AGI grade 0–I criteria are randomized (1:1) to one of two intervention arms: continuous Peptide-Based Enteral Formula Group (PBF group) and Sequential Standard Polymeric Enteral Formula Group (SPF group). All other aspects of ICU care follow contemporary best practice and local guidelines. Table 1 shows the schedule of enrolment, interventions, and assessments based on the SPIRIT 2013 statement (14). Detailed reporting checklists are provided in the Supplementary Table S2 (SPIRIT 2013 checklist).

**Table 1 tab1:** Schedule of enrolment, interventions, and assessments.

[figure not shown]

PBF group, Continuous Peptide-Based Enteral Formula Group; SPF group, Sequential Standard Polymeric Enteral Formula Group.

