#### Secondary outcome definition and measures

2.7.2

Protein intake on Day 7, defined as the actual protein delivered on study Day 7 (g/kg/day). For patients with BMI > 30 kg/m^2^, an AdjBW will be used.Occurrence of FI between ICU days 4–7, FI is defined as (6) present if any of the following criteria are met: ① Vomiting: any visible regurgitation of gastric contents, irrespective of volume. ② High gastric residual volume (GRV): any single GRV > 200 mL. ③ Diarrhea: ≥3 loose or liquid stools per day and stool weight >200–250 g/day or volume >250 mL/day. ④ Gastrointestinal (GI) bleeding: any intraluminal GI bleeding confirmed by gross blood in vomitus, gastric aspirate, or stool. ⑤ Insufficient enteral energy delivery: failure to achieve ≥20 kcal/kg body weight/day via the enteral route within 72 h after initiation/attempt of enteral feeding. ⑥ Cessation of enteral nutrition: enteral feeding discontinued for any clinical reason. Outcome recording. The presence or absence of FI will be assessed once per day on ICU days 4–7. In addition to the composite FI outcome, individual FI components will be reported and analyzed separately.Change in nutritional biomarkers. Defined as serum albumin and prealbumin concentrations measured on study day 1 (baseline) and day 7. Reporting values (albumin in g/L; prealbumin in mg/L) at each time point; change calculated as Day 7 − Day 1.Skeletal muscle status. Muscle mass change will be assessed using the following sonographic metrics on ICU days 1, 4, and 7 after admission: upper-limb muscle thickness; quadriceps muscle thickness; rectus femoris cross-sectional area (RF-CSA).Intestinal injury biomarkers. Between-group differences in intestinal injury markers will be evaluated using serum/plasma concentrations of D-lactate, intestinal fatty-acid binding protein (I-FABP), and diamine oxidase (DAO) on study Day 1 and Day 7. *Measurement & reporting:* assays performed per manufacturer instructions; values reported in assay-specified units. Changes from baseline (Day 7–Day 1) and between-group differences in change will be analyzed.New infections in the ICU: Defined as infections newly acquired ≥48 h after ICU admission.ICU length of stay.Ventilator-free days: Ventilator-free days within 28 days in the ICU.ICU hospitalization cost. Defined as the total direct medical cost accrued during the index ICU stay, from ICU admission (time 0) to ICU discharge. Extracted from the hospital billing system/financial data warehouse using patient identifiers and ICU encounter numbers.28-day mortality: Assessed on day 28 after ICU admission.90-day mortality: Assessed on day 90 after ICU admission.

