##### Exposure metrics

2.7.5.1

All participants receive a short-peptide formula from enrollment through study Day 3; this run-in period is not included in exposure analyses and is used solely for baseline standardization and tolerance assessment. Randomization occurs on Day 4 (D4). The exposure assessment window is D4–D7. We will record:

Duration of the exposure window (hours): elapsed time from randomization (D4) to 23:59 on D7 or to ICU transfer/discharge or death, whichever occurs first.Concordant feeding hours: cumulative hours during which the randomized formulation was actually administered.Adherence (%) = (concordant feeding hours ÷ exposure window hours) × 100. Interruptions (e.g., procedures, intolerance) will be time-stamped; calculations use actual accrued hours within the window.

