Experimental studies in rats (19–21) indicate that exposure of the colon to N-formyl-methionyl-leucyl-phenylalanine (fMLP) increases the expression of oligopeptide transporters, e.g., Peptide Transporter (PEPT) family, which may aggravate colonic mucosal injury. PBFs could confer a gastrointestinal protective effect by competitively inhibiting fMLP transport and/or leveraging higher transport efficiency through the same carriers, thereby reducing epithelial damage. Additional evidence suggests that (10), compared with SPFs, PBFs accelerate intestinal digestion and absorption of protein, enhance postprandial amino-acid availability, and may increase the rate of skeletal-muscle protein synthesis. Our prior work further showed that (8, 22), versus SPFs, PBFs enabled faster achievement of nutritional targets via EN and were associated with a lower incidence of feeding intolerance. Recent evidence from our team (13) in patients with AGI grade I–II who initiated EN within 48 h, PBFs were associated with greater caloric adequacy and lower incidences of gastric residuals and diarrhea; conversely, among those who initiated EN between days 3–7, SPFs achieved higher caloric adequacy, with no significant differences in gastric residuals or diarrhea between group. These data imply a time-dependent formula preference—PBFs may be more appropriate early, whereas SPFs may be preferable on days 3–7. However, because the study was retrospective, selection bias related to baseline gastrointestinal function cannot be excluded. Accordingly, we designed a prospective, randomized, controlled study to further evaluate, among AGI grade I–II patients who receive PBFs feeding for the first 3 days and whose intestinal function recovers to or remains at AGI 0–I, whether continuing PBFs versus switching to SPFs from day 4 differs in caloric and protein intake, nutritional biomarkers, and intestinal injury markers. We also planned to assess trajectories of muscle mass to clarify whether peptide formulas better support muscle protein synthesis and mitigate muscle loss in critical illness. Key clinical outcomes include mortality, ICU length of stay, ventilator-free time, and the incidence of ICU-acquired infections. Overall, this study will compare the two formulas across nutritional adequacy, feeding tolerance, intestinal protection, muscle preservation, and clinical outcomes, providing clinically meaningful evidence.

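### The five blood markers are sampled on Day 1 and Day 7 although the arms part on Day 4: half the change interval is common run-in, which costs precision but does not bias the comparison

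*Protocol article*

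**What the plan says.** Section 2.7.2 fixes both the sampling days and the subtraction. The nutritional markers are "Defined as serum albumin and prealbumin concentrations measured on study day 1 (baseline) and day 7", with change taken as Day 7 minus Day 1. The intestinal injury markers are D-lactate, "intestinal fatty-acid binding protein (I-FABP), and diamine oxidase (DAO) on study Day 1 and Day 7", and for these "Changes from baseline (Day 7–Day 1) and between-group differences in change will be analyzed".

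The arms separate later. Under Study interventions (2.6), every patient receives the peptide formula on study days 1–3; those at AGI grade 0–I on Day 4 are then randomised. Section 2.7.5.1 states that "The exposure assessment window is D4–D7". The Discussion puts the question as "whether continuing PBFs versus switching to SPFs from day 4 differs in caloric and protein intake, nutritional biomarkers, and intestinal injury markers".

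Muscle ultrasound is scheduled on days 1, 4 and 7 (2.6.4 and 2.7.2), so a Day-4 research assessment already exists. The outcome definitions mention no Day-4 blood sample. Section 2.8.2 analyses continuous secondary outcomes by linear regression with group, APACHE II, BMI, AGI grade and primary diagnosis; a marker's own baseline is not among the named covariates.

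**The concern.** The trial asks what happens from Day 4, but the blood markers are measured from Day 1. The planned change therefore adds three days of randomised treatment to three days in which both arms were fed alike. Those first three days also contain whatever improvement brought some patients to AGI grade 0–I, the condition for randomisation, and gut-injury markers may well track it.

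Three things are at stake. The comparison carries patient-to-patient variation from Days 1 to 4 that has nothing to do with allocation. Marker balance at randomisation cannot be described. And a fall or rise within an arm from Day 1 to Day 7 cannot be attributed to continuing or switching. All of this concerns secondary outcomes; the primary outcome, energy intake on Day 7, is untouched.

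**Working it through.** The article gives no SD, correlation or sample size for any marker, so there is no figure of the plan's own to reproduce. The days come from 2.6, 2.7.2 and 2.7.5.1; the correlations are assumptions.

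**1. Timeline.** Change interval: 7 − 1 = 6 days. Common run-in: 4 − 1 = 3 days. Share before randomisation: 3/6 = 50%.

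**2. Bias.** Write (Day 7 − Day 1) = (Day 7 − Day 4) + (Day 4 − Day 1). The second term precedes randomisation, so its expectation is the same in both arms and it cancels from the between-arm difference. A simulation agrees (true effect 0.30 SD, 225 per arm, assumed correlation 0.8 between Days 4 and 7 and 0.8² = 0.64 between Days 1 and 7):

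- Day 7 − Day 1: mean estimate 0.300, standard error 0.080.
- Day 7 − Day 4: mean estimate 0.301, standard error 0.061.

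The two give the same answer with different precision.

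**3. Precision.** Assume equal variances (set to 1) and correlation r per day, so that ρ(4,7) = r³ and ρ(1,7) = r⁶. A raw change score has variance 2(1 − ρ). A Day-7 value adjusted for baseline has residual variance 1 − ρ². The ratio of adjusted variances, Day 4 to Day 1, is (1 − r⁶)/(1 − r¹²) = 1/(1 + r⁶).

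| r per day | Change from Day 1 | Change from Day 4 | Adjusted for Day 1 | Adjusted for Day 4 | Adjusted ratio, Day 4 / Day 1 |
|---|---|---|---|---|---|
| 0.60 | 1.907 | 1.568 | 0.998 | 0.953 | 0.96 |
| 0.70 | 1.765 | 1.314 | 0.986 | 0.882 | 0.89 |
| 0.80 | 1.476 | 0.976 | 0.931 | 0.738 | 0.79 |
| 0.90 | 0.937 | 0.542 | 0.718 | 0.469 | 0.65 |
| 0.95 | 0.530 | 0.285 | 0.460 | 0.265 | 0.58 |

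Example, r = 0.80: r⁶ = 0.262 and r¹² = 0.069, so 0.738/0.931 = 0.79.

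The table shows three things:

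- With adjustment, the gain from a Day-4 baseline runs from about 4% (r = 0.60) to 42% (r = 0.95).
- If correlation does not decay with time, ρ(1,7) = ρ(4,7), the ratio is 1.00 and nothing is gained.
- The raw change from Day 1 is the least precise choice in every row. Since 2(1 − ρ) exceeds 1 when ρ is below 0.5, it is then worse than the Day-7 value alone; here that is so for r = 0.60, 0.70 and 0.80.

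**The case against.** The strongest reply is that randomisation already protects the comparison. It does: a reader might infer that the effect from Day 4 cannot be estimated from samples on Days 1 and 7, and step 2 shows that this is wrong.

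A reader might also see a contradiction with 2.7.5.1, which says of the run-in that "this run-in period is not included in exposure analyses and is used solely for baseline standardization and tolerance assessment". That sentence stands under exposure metrics and governs feeding hours and adherence, not outcome baselines. There is no contradiction.

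The selection argument should not be pressed either. Grade I is admissible at entry, so a randomised patient need not have improved, and selection precedes allocation and acts on both arms alike. Nor does the article say that within-arm changes will be read as formula effects; it plans between-group comparisons and promises cautious interpretation.

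On size, the gain rests wholly on an assumed decay of correlation. Part of the loss can be recovered without any new sample: at r = 0.80, adjusting Day 7 for the existing Day-1 value (0.931) does slightly better than a raw change from Day 4 (0.976). At r = 0.90 and 0.95 the order reverses (0.718 against 0.542; 0.460 against 0.285).

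Finally, the schedule in Table 1 is not shown and might list a Day-4 sample, though the outcome definitions would still not use it. Recruitment status is not stated, so the number of patients who could benefit is unknown. For muscle, the Day-4 scan is already planned; which interval is modelled is detail an article may leave to the analysis plan.

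All these replies stand. They reduce the point to precision and interpretability; they do not remove it.

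**Conclusion.** The point holds as a design improvement on secondary outcomes. Half of the defined change interval precedes any difference between arms, and the text defines no marker value at randomisation. The between-arm estimate is unbiased.

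The cost in precision cannot be fixed from the article. Under equal variances and correlation decaying by r per day, adjusted residual variance with a Day-4 baseline is 0.96, 0.89, 0.79, 0.65 and 0.58 of that with a Day-1 baseline for r = 0.60, 0.70, 0.80, 0.90 and 0.95. Under constant correlation it is 1.00. Whatever the correlation, within-arm changes from Day 1 cannot be read as effects of continuing or switching.

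**What to change.** - **Patients still to be enrolled:** take the baseline sample for the five markers on Day 4, before the first assigned formula, in place of Day 1. Analyse the Day-7 value with the Day-4 value as a covariate, rather than a raw change score.
- **Patients with only a Day-1 sample:** analyse Day 7 adjusted for Day 1. In a joint model, include a baseline-day indicator and its interaction with the baseline value. Do not pool 6-day and 3-day change scores.
- **Muscle:** use the existing Day-4 scan as the baseline covariate for Day 7.
- **Reporting:** if sampling stays as it is, adjust Day 7 for Day 1 and state that Day 1 precedes the run-in.

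The cost is a schedule and wording amendment. The number of assays per randomised patient is unchanged, patients who are never randomised need no baseline assay, and the muscle change needs no new measurement. The downside is losing the Day-1 research-assay picture, or one extra tube per patient if both days are kept.

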#### Data analysis

2.8.2

All statistical analyses will be conducted in accordance with a pre-specified statistical analysis plan. The primary analysis will follow the intention-to-treat (ITT) principle The Full Analysis Set (FAS) will include all participants who were successfully randomized and entered the intervention period, provided that they have a valid assessment of the primary outcome (caloric intake on day 7) or sufficient information to derive this value. The Per Protocol Set (PPS) will be a subset of the FAS, including participants who received the allocated intervention for at least 72 h and had no major protocol deviations. The PPS will be used for sensitivity analyses to assess the robustness of the primary findings. The SS will include all participants who received at least one dose of the study intervention and will be used for safety analyses.

The primary outcome, caloric intake on day 7 (continuous variable), will be analyzed using a linear regression model. The model will include the intervention group and the predefined covariates (APACHE II score, BMI, AGI grade, and primary diagnosis) as fixed effects. As this is a single-center randomized controlled trial, no random effects will be specified. To account for potential model misspecification and heteroscedasticity, heteroskedasticity-robust (sandwich) standard errors will be used for statistical inference. If the model residuals show substantial deviation from normality or are influenced by outliers, data transformation (for example, logarithmic transformation) or a nonparametric bootstrap method will be applied in sensitivity analyses to assess the robustness of the results.

Continuous secondary outcomes (e.g., the number of days without a ventilator in the ICU) will be analyzed analogously using linear regression models; secondary binary outcomes (e.g., FI) will be analyzed using a generalized linear model (GLM) with a logit link function. The model will include the intervention group and the pre-specified covariates as fixed effects. As this is a single-center study without inter-center or clustering structures, no random effects will be specified. In addition, because FI is a composite secondary endpoint, each FI component will be reported and analyzed separately alongside the composite FI outcome.

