Continuous variables will be summarized as mean ± SD if normally distributed, or as median and interquartile range (IQR, P25–P75) if not normally distributed. Between-group differences in continuous variables will be tested using the independent samples t-test for normally distributed data or the Mann–Whitney U test for non-normally distributed data. Categorical variables will be compared using the Chi-square test.

To assess whether between-group differences in caloric adequacy and tolerance reflect intrinsic physiological effects of the enteral formulas or are confounded by differences in feeding tolerance management, we will compare key nutrition-support process indicators (time to EN initiation; FIS-guided feeding-rate adjustments every 4–6 h; use of prokinetic and/or anti-diarrheal agents; post-pyloric feeding) between groups during the intervention period and will add these as covariates for adjusting confounding factors. At the same time, we will conduct sensitivity analyses to test the robustness of the results.

Sensitivity analyses will include: (I) an unadjusted GLM including only the treatment factor; (II) a covariate-augmented GLM including the prespecified covariates APACHE II score, AGI grade, BMI, primary diagnosis as well as baseline mechanical ventilation. (III) Key treatment indicators include time to initiation of enteral nutrition, feeding-rate adjustments at 4–6-h intervals based on the FIS score, use of prokinetics or antidiarrheals, and use of post-pyloric feeding. All covariates are prespecified and will be retained in the models regardless of statistical significance.

Adjusted odds ratios (ORs) with 95% confidence intervals (CIs) will be reported for binary outcomes, with standardized marginal risk differences provided as supplementary estimates. The primary endpoint will be tested at a two-sided *α* = 0.05 level without multiplicity adjustment. For prespecified secondary clinical endpoints, the false discovery rate (FDR) will be controlled at q = 0.05 using the Benjamini–Hochberg procedure based on two-sided *p* values from the specified models.

Process outcomes (such as fidelity, exposure, and contamination) will be treated as exploratory outcomes and summarized descriptively with 95% CIs; no hypothesis testing or multiplicity correction will be applied to these exploratory analyses.

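### D-lactate, I-FABP and DAO are analysed as untransformed change without the Day-1 value as covariate, which keeps type I error but gives up power

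*Protocol article*

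**What the plan says.** Section 2.7.2 of the protocol article measures D-lactate, I-FABP and DAO on study Days 1 and 7, with "values reported in assay-specified units". It then fixes the quantity to be analysed: "Changes from baseline (Day 7–Day 1) and between-group differences in change will be analyzed".

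Section 2.8.2 fixes the model: "Continuous secondary outcomes (e.g., the number of days without a ventilator in the ICU) will be analyzed analogously using linear regression models". The primary-outcome model that this refers to contains the group and the "predefined covariates (APACHE II score, BMI, AGI grade, and primary diagnosis) as fixed effects". The baseline marker value is not among them.

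The plan makes three provisions for non-normal data, all in section 2.8.2:
- For the primary model, "heteroskedasticity-robust (sandwich) standard errors will be used for statistical inference".
- If that model's residuals depart substantially from normality or outliers are influential, "data transformation (for example, logarithmic transformation) or a nonparametric bootstrap method will be applied in sensitivity analyses".
- For between-group differences in continuous variables generally, it names the "Mann–Whitney U test for non-normally distributed data".

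The same section bases the false-discovery-rate procedure for secondary clinical endpoints on p values from the specified models. If the markers count among those endpoints, the regression result decides.

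**The concern.** Two features of the planned analysis can cost precision.

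The first is the change score. If Day-1 and Day-7 values have equal variance σ² and correlation ρ, the change has variance 2σ²(1 − ρ). Adjusting for baseline leaves σ²(1 − ρ²). The ratio is 2/(1 + ρ), which always favours adjustment. When ρ is below 0.5, the change is noisier than the Day-7 value alone. Here Day 1 lies before a three-day run-in and a selection on AGI grade at Day 4, so a modest correlation is plausible, though the article gives no figure.

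The second is the scale. If the concentrations have a long right tail, a few high values dominate a mean difference in assay units and its standard error.

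The Discussion names intestinal protection as one of the comparisons the trial will make, and these three markers are its direct measurement. A null result on raw change could then reflect the analysis and not the formula.

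**Working it through.** **No figure to reproduce.** The article states no SD, skewness, correlation, effect or power for the markers. What follows rests on assumptions and is shown as a range.

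**Inputs from the article.** Planned N is 496 with 1:1 allocation (section 2.5). About 15% missing data are expected for Day-7 caloric intake (section 2.8.3), assumed here to apply to Day-7 samples as well. That gives 496/2 × 0.85 = 210.8, about 211 per arm. Two-sided alpha is 0.05, without the false-discovery-rate step.

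**Assumed.** Lognormal markers, equal Day-1 and Day-7 medians without an effect, log SD σ of 0.5 to 1.0, log-scale correlation ρ of 0.2 to 0.7. The effect is multiplicative (Day-7 ratio r), set so that the baseline-adjusted log analysis has 80% power. The four prognostic covariates are left out.

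**One cell by hand (σ = 0.8, ρ = 0.3).**
1. Log analysis with log baseline: SE = 0.8 × √(1 − 0.09) × √(2/211) = 0.0743. For 80% power, ln r = −(1.960 + 0.8416) × 0.0743 = −0.208, so r = 0.812.
2. Log change: the detectable z of 2.80 is divided by √(2/1.3) = 1.240, giving 2.26. Power = Φ(2.26 − 1.96) = 62%.
3. Raw change, in units of the control mean: variance V = e^0.64 − 1 = 0.8965 and covariance C = e^0.192 − 1 = 0.2117. Variance of change is 2V − 2C = 1.370 in one arm and V(1 + r²) − 2rC = 1.144 in the other. SE = √((1.370 + 1.144)/211) = 0.109. The effect is 1 − 0.812 = 0.188, so z = 1.72 and power = Φ(1.72 − 1.96) = 41%.

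**Simulation over the range** (1,500 trials per cell, robust standard errors; power in %):

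| log SD | ρ | raw change | raw change, Day-1 covariate | Mann–Whitney on raw change | log change | log Day 7 on log Day 1 |
|---|---|---|---|---|---|---|
| 0.5 | 0.2 | 48.9 | 73.5 | 51.2 | 59.1 | 79.6 |
| 0.5 | 0.7 | 61.5 | 71.9 | 64.7 | 72.3 | 79.3 |
| 0.8 | 0.2 | 38.5 | 63.9 | 45.8 | 57.2 | 78.1 |
| 0.8 | 0.3 | 41.2 | 64.8 | 52.9 | 61.7 | 80.1 |
| 0.8 | 0.7 | 46.6 | 58.7 | 63.3 | 72.4 | 79.9 |
| 1.0 | 0.2 | 32.1 | 59.5 | 47.3 | 60.0 | 80.5 |
| 1.0 | 0.7 | 40.9 | 51.0 | 60.5 | 73.1 | 79.2 |

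The row for 0.8 and 0.3 agrees with the hand calculation.

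**Where the gap comes from.** At log SD 0.5 and ρ 0.2, adding the Day-1 value on the raw scale closes (73.5 − 48.9)/(79.6 − 48.9) = 80% of the gap. At 0.8 and 0.3 it closes (64.8 − 41.2)/(80.1 − 41.2) = 61%. At 1.0 and 0.7 it closes (51.0 − 40.9)/(79.2 − 40.9) = 26%. The rest is scale.

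**Fixed effect.** With 205 per arm, a 20% reduction, log SD 0.8 and ρ 0.3–0.5, power is 45–57% for raw change, 69–76% for raw with baseline and 84–91% for log with log baseline.

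**Type I error** of raw change is 4.5–5.2%.

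**A different effect shape.** With 190 per arm, log SD 0.8, ρ 0.3–0.5 and a 40% reduction only in Day-7 values above the upper quartile, power is 52–58% for raw change, 84–90% for raw with baseline, 30–33% for log change and 42–49% for log with log baseline. Here the log scale loses, while the baseline term still helps.

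**The case against.** The strongest objection is that the premise lies outside the article. Nothing there says that these markers are right-skewed or that a formula effect would be multiplicative, and the ranking of the two scales depends on both. This stands: the log scale loses clearly when only the upper tail is lowered. The case for the baseline covariate does not depend on it, since that term helped in every scenario tried.

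Second, the plan does provide for non-normality, and a reader might infer from the raw change score that it does not. That would be unfair. But robust standard errors protect the error rate and do not restore power. The log or bootstrap option is conditional, confined to sensitivity analyses and written for the primary outcome. Mann–Whitney on raw change reaches 46–65% in the cells tabulated, against about 80%.

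Third, transformation of individual biomarkers is often left to the statistical analysis plan, which is not shown. That would answer silence. Here the article states the quantity, the units, the model and the covariates, so it is a stated choice.

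Fourth, these are secondary markers, no power is claimed for them, and section 2.8.2 promises cautious interpretation. This stands and limits the weight of the point.

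**Conclusion.** The point holds as one of efficiency. The planned marker analysis is valid but weaker than it need be. Under right skew with log SD 0.5–1.0, correlation 0.2–0.7 and a multiplicative effect, raw change has about 32–62% power where the baseline-adjusted log analysis has 80%. The omitted Day-1 value accounts for about a quarter to four fifths of that gap in the cells worked above.

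Three stronger readings are not supported:
- A reader might infer that half the power is lost, or that half is the most that can be lost. No such figure follows from the article. Over a wider set of assumptions (log SD 0.3–1.2, reference power 80% or 90%), the relative loss runs from 11% to 67%.
- A reader might put the whole loss down to skewness. Much of it is the missing baseline covariate.
- A reader might conclude that the marker results would be biased or their tests invalid. Type I error stays near 5%.

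**What to change.** For D-lactate, I-FABP and DAO, state as the main model a linear regression of log Day-7 concentration on group, log Day-1 concentration and the prespecified covariates. Report the ratio of geometric means with its 95% CI, and keep the Day 7 minus Day 1 change in assay units as a descriptive summary. Report the baseline-adjusted raw-scale model as a sensitivity analysis, because the log scale can lose power if the formula mainly lowers the highest values. If the sponsor prefers assay units throughout, the minimum change is to add the Day-1 marker value as a covariate.

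The cost is a change of wording in the analysis plan, made before the marker data are analysed so that the scale is not chosen after seeing residuals. No extra samples or patients are needed. The price is that the effect is read as a ratio and not as a difference in units.

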##### Inclusion criteria

(1) Age ≥18 years.(2) ICU admission with AGI grade I (gastrointestinal dysfunction with risk of failure) or grade II (gastrointestinal dysfunction) according to the 2012 European Society of Intensive Care Medicine (ESICM) (6) diagnostic criteria.(3) Able to initiate enteral nutrition within 24–48 h of ICU admission.

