### Randomization and blinding methods

2.4

Because all enrolled patients initially present with AGI grade I–II, a PBF will be administered for the first 3 study days. On day 4 of the study, gastrointestinal function will be reassessed. Patients reassessed as AGI grade 0–I will be eligible for randomization. Eligible patients will be randomized using block randomization, with a 1:1 allocation ratio to either continued a PBF (PBF group) or transition to an SPF (SPF group). The randomization sequence will be generated in R software (version 4.4.2) using permuted blocks of variable size (4 and 6).

Owing to the nature of the intervention, this is an open-label protocol, and the treating clinical team must be aware of group assignment for intervention delivery (participants may or may not be aware depending on clinical status). To minimize detection bias, feeding intolerance and other outcomes will be assessed and recorded by dedicated research staff who are independent from the ICU clinical team and do not participate in treatment decisions or nursing care.

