#### Arm#2: Sequential Standard Polymeric Enteral Formula Group (SPF group)

2.6.2

Intervention. Transition from a PBF to an SPF after randomization.

Administration mode. Continuous pump infusion (gastric or post-pyloric).

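### New ICU infections are timed from ICU admission alone, so infections acquired between 48 h and the Day 4 randomisation count as trial outcomes

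*Protocol article*

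**What the plan says.** The protocol article, section 2.7.2, defines new infections in the ICU as "infections newly acquired ≥48 h after ICU admission". ICU admission is the only clock in that definition.

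Allocation comes later. Section 2.4 states that "a PBF will be administered for the first 3 study days", and section 2.7.5.1 that "Randomization occurs on Day 4 (D4"). The arms differ only from then on: for the SPF arm, section 2.6.2 specifies "Transition from a PBF to an SPF after randomization".

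Two neighbouring rules are aligned with randomisation. Feeding intolerance, also in section 2.7.2, is assessed as "Occurrence of FI between ICU days 4–7". For exposure, section 2.7.5.1 says of the run-in that "this run-in period is not included in exposure analyses and is used solely for baseline standardization and tolerance assessment". That exclusion covers exposure analyses; it says nothing about counting outcomes.

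The Discussion lists ICU-acquired infection among the key clinical outcomes. Section 2.8.2 places prespecified secondary clinical endpoints under false discovery rate control at q = 0.05.

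**The concern.** The 48 h rule separates infections acquired in the ICU from those already present or incubating on admission. It does not separate events before allocation from events after it. In a trial that randomises at admission, one rule nearly does both jobs. Here randomisation is delayed to Day 4, so a second condition is needed, and the article does not give one.

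A patient who develops pneumonia at 60 h and is randomised at 90 h meets the definition and is an event in the allocated arm. Both arms were then on the same formula, so the event carries no information on the comparison. The exclusion criteria do not remove such a patient.

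At stake is the sensitivity of a formally tested secondary outcome. Events fixed before allocation pull the estimated ratio towards 1 and add chance variation. If infection is analysed as a yes/no outcome per patient, a run-in infection also hides any later infection in that patient.

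**Working it through.** The article gives no infection rate, expected effect or power for this outcome, so there is no figure to reproduce. The check has two parts: the overlap, which follows from the text, and its effect, which needs assumptions.

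**1. Overlap**

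Overlap = time from ICU admission to randomisation − 48 h.

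*Study days follow ICU days.*
- In elapsed time, Day 4 starts at 3 × 24 = 72 h, giving 72 − 48 = 24 h. It ends at 96 h, giving 48 h.
- In calendar days, a late-evening admission on Day 1 puts the start of Day 4 just over 48 h later, so the overlap is about 0 h. Admission at noon on Day 1 with randomisation at 09:00 on Day 4 is 12 + 24 + 24 + 9 = 69 h, giving 21 h.
- The range is therefore about 0–48 h, typically about 24 h.

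*Study Day 1 begins with feeding.* The inclusion criterion reads "Able to initiate enteral nutrition within 24–48 h of ICU admission".
- Start at 24 h: Day 4 starts at 24 + 72 = 96 h, giving 48 h.
- Start at 48 h: Day 4 starts at 48 + 72 = 120 h, giving 72 h.

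The article does not settle which applies. Sections 2.4 and 2.6 speak of study days, while the abstract's interventions paragraph and the feeding-intolerance definition speak of ICU days. The abstract also gives a 7-day limit for starting the peptide formula, which does not match the inclusion criterion. Those passages need reconciling; I used the inclusion criterion. On every reading the definition admits infections from a point at or before randomisation.

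**2. Effect on the estimate (assumptions, not document figures)**

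Assume a constant infection hazard from 48 h to ICU discharge, a stay of L days, an overlap of d days and a true post-randomisation rate ratio of 0.70.

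- Share of reference-arm infections before randomisation: s = d / (L − 2)
- Apparent rate ratio: s + (1 − s) × 0.70

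| d | L = 7 | L = 10 | L = 14 |
|---|---|---|---|
| 1 day | s = 1/5 = 20%; ratio 0.76 | s = 1/8 = 12.5%; ratio 0.74 | s = 1/12 = 8%; ratio 0.73 |
| 2 days | s = 40%; ratio 0.82 | s = 25%; ratio 0.78 | s = 17%; ratio 0.75 |
| 3 days | s = 60%; ratio 0.88 | s = 37.5%; ratio 0.81 | s = 25%; ratio 0.78 |

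The 1-day row matches the typical overlap when study days follow ICU days.

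**3. The same effect on a yes/no outcome**

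Assume post-randomisation risks of 20% and 12%, and a proportion q in each arm already infected during run-in. The counted risk is q + (1 − q)p.
- q = 0: 20% v 12%; risk ratio 0.60, difference 8.0 points.
- q = 2%: 21.6% v 13.8%; risk ratio 0.64, difference 7.8 points.
- q = 5%: 24.0% v 16.4%; risk ratio 0.68, difference 7.6 points.

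The direction is the same, and the ratio moves more than the difference.

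**The case against.** The strongest reply is that 48 h after ICU admission is a case definition for ICU-acquired infection, not a statement of when counting opens. On that view a condensed article may leave the counting window to the full protocol or analysis plan. This stands in part: the fuller documents may contain a lower limit. But the article does not simply leave the matter open. It states what makes an infection new, ties it to ICU admission, and nowhere excludes the interval before randomisation. Followed as printed, the rule counts those events.

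A second reply is that mortality and length of stay also run from ICU admission. They are not comparable: no randomised patient can have died before randomisation, and length of stay carries earlier time rather than a completed event.

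Third, the impact may be small, and this stands. On calendar days the overlap can be close to nothing. Only patients at AGI grade 0–I on Day 4 are randomised, so some with a serious run-in infection may never enter. The article also does not say whether infection is analysed as a yes/no outcome or as a count, so the masking of later infections is conditional.

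A reader might go further and infer that early infections fall in the period of highest risk, so that dilution is large. Nothing in the article supports this, and it would contradict the constant hazard used above.

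**Conclusion.** The point holds. The infection outcome has a time origin that does not suit a Day 4 randomisation, and infections between 48 h and randomisation count although allocation cannot have affected them.

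The overlap follows from the text, within the uncertainty about study days and ICU days. The dilution figures rest on an assumed hazard, length of stay and effect. With the 1-day overlap they are modest: about 8–20% of counted infections, and 0.70 seen as about 0.73–0.76. Longer overlaps dilute more. The 60% cell in the table should not be taken as the expected size: it needs study Day 1 to begin 48 h after admission and every stay to last only 7 days.

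A reader might also infer that the comparison is biased in favour of one formula. It is not: events before allocation are balanced in expectation, so the consequence is dilution and noise. The primary endpoint, energy intake on Day 7, is untouched. This is a worthwhile correction to one secondary outcome, not a threat to the trial's main conclusion.

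**What to change.** Amend the definition in section 2.7.2 along these lines: a new ICU infection is one with onset after randomisation that also occurs at least 48 h after ICU admission. Infections arising between 48 h and randomisation are recorded as a baseline characteristic. A later, distinct infection in the same patient still counts, and no randomised patient is dropped because of a run-in infection. If the full protocol or analysis plan already sets this limit, it is enough to state it.

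The cost is one or two sentences in the definition. Infection onset dates must be recorded; the article does not say whether they are. Somewhat fewer events will be counted, but those removed say nothing about the effect of the formula.
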